# Improving access to medicines for non-communicable diseases in rural India: a mixed methods study protocol using quasi-experimental design

**DOI:** 10.1186/s12913-016-1680-3

**Published:** 2016-08-22

**Keywords:** Non-communicable diseases, Health systems research, Access to medicines, Out-of-pocket expenditure on medicines

## Abstract

**Background:**

India has the distinction of financing its healthcare mainly through out-of-pocket expenses by individual families contributing to catastrophic health expenditure and impoverishment. Nearly 70 % of the expenditure is on medicines purchased at private pharmacies. Patients with chronic ailments are especially affected, as they often need lifelong medicines. Over the past years in India, there have been several efforts to improve drug availability at government primary health centres. In this study, we aim to understand health system factors that affect utilisation and access to generic medicines for people with non-communicable diseases.

**Methods:**

This study aims to understand if (and how) a package of interventions targeting primary health centres and community participation platforms affect utilisation and access to generic medicines for people with non-communicable diseases in the current district context in India. This study will employ a quasi-experimental design and a qualitative theory-driven approach. PHCs will be randomly assigned to one of three arms of the intervention. In one arm, PHCs will receive inputs to optimise service delivery for non-communicable diseases, while the second arm will receive an additional package of interventions to strengthen community participation platforms for improving non-communicable disease care. The third arm will be the control. We will conduct household and facility surveys, before and after the intervention and will estimate the effect of the intervention by difference-in-difference analysis. Sample size for measuring effects was calculated based on obtaining at least 30 households for each primary health centre spread across three distance-based clusters. Primary outcomes include availability and utilisation of medicines at primary health centres and out-of-pocket expenditure for medicines by non-communicable disease households. Focus group discussions with patients and in-depth interviews with health workers will also be conducted. Qualitative and process documentation data will be used to explain how the intervention could have worked.

**Discussion:**

By taking into consideration several health system building blocks and trying to understand how they interact, our study aims to generate evidence for health planners on how to optimise health services to improve access to medicines.

**Trial registration:**

Protocol registered on Clinical Trials Registry of India with registration identifier number CTRI/2015/03/005640 on 17^th^ March 2015.

**Electronic supplementary material:**

The online version of this article (doi:10.1186/s12913-016-1680-3) contains supplementary material, which is available to authorized users.

## Background

### Access to medicines

The first point of contact for curative services in India is typically in the private sector, and often with medical practitioners without a formal medical degree in modern medicine [1–3]. In most Indian cities and in rural areas, private healthcare providers manage patients with chronic diseases deepening health insecurity for the poor [4, 5]. Even in cases where patients obtain outpatient care in government hospitals, they often have to purchase medicines from private pharmacies, either due to frequent stock-out of medicines at primary health centres (PHC), or poor procurement and distribution of drugs at higher levels [6, 7]. In spite of recent efforts through the National Rural Health Mission to improve utilisation of public services and decrease out-of-pocket expenditure (OOP) on medicines, recent estimates of OOP expenditure on medicines continues to be as high as 70 %, with instances of people falling into poverty merely from paying for outpatient care for non-communicable diseases (NCD) [8–10].

The poor availability of drugs in public services is further complicated by inadequate availability of relatively inexpensive branded or unbranded generic alternatives in the private pharmacies [11]. In spite of India’s reputation as a global supplier of generic drugs, widespread reports of spurious medicines and the lack of an effective regulatory system for medicines affect people’s perceptions of quality of these drugs [12–14]. In addition, leadership and management of government health services at various levels within the health system influences access to medicines. The ways in which health systems organise their governance, resources use, organisation and management of services as well interact with people are being identified as the crucial in ensuring access to medicines, especially in public services [15] (see Fig. 1). Recent efforts at making available cheaper generic equivalents of essential drugs through *Jan Aushadhi* stores (people’s pharmacy in Hindi) have shown promising results; the generic drugs supplied have been reported to be comparable in quality to their proprietary equivalents [16, 17].

**Fig. 1 Fig1:**
[figure not shown]
Problem tree illustrating government health services problems that could drive NCD patients to buy essential drugs from private pharmacies

### Medicines and primary health care

Among the several approaches to organising care for NCDs in low- and middle-income countries (LMIC), the underlying principle is a well-performing primary health care system that ensures access to essential drugs for treatment of NCDs [18, 19]. Ensuring availability of medicines in government PHCs is necessary, but not sufficient to ensure access to medicines. Several factors ranging from individual and household perceptions, societal preferences and health-seeking behaviour to other factors related to health system, including availability, but also affordability, quality and management of government health services together characterise a well-performing health system. A systemic perspective on how these various factors interact is crucial in strengthening public services response to NCDs.

In this study, we aim to study the health system factors at the sub-district and PHC level that influence access to medicines for people with NCDs (diabetes and hypertension) in a rural Indian district setting. In doing so, we seek to understand how a mixed public-private health system, which is in the process of strengthening and decentralisation, such as the one in India responds to health services strengthening interventions to improve access to medicines.

### Rationale of the study: medicines and NCDs in India

Globally, there has been a lot of focus on the challenges in organising care for NCDs, especially in LMICs [18]. Recent publications highlight the inability of several LMIC health systems to deal with the rising needs of continuous care and follow-up required for patients with NCDs, as opposed to sporadic and episodic care for infectious diseases [20, 21]. There is increasing pressure on Indian policymakers at all levels to improve services for people with NCDs. Recently, a vertical programme, the *National programme for control of cancer*, *diabetes*, *cardiovascular diseases and stroke* (NPCDCS) was launched by the Indian government to address this challenge [22]. Various state governments in India as well as the national government have responded favourably through policies to improve access over the last decade. We take into consideration the following factors related to the policy environment within which this study is being proposed, thus of importance to the design of the study and, eventually for the interpretation of its results.

The governments of India and Karnataka have committed to investing more money in purchasing generic medicines and improving availability of these in government-funded/operated generic drug pharmacies [23, 24].

Recent reforms in Indian government health services through the National Health Mission (NHM) encourage community involvement in managing and financing primary health centres (PHC) through the establishment of *Arogya Raksha Samitis* (patient welfare committees). These committees have a mandate to oversee the PHC activities, as well as receive financial endowments from the State for improvements in PHC services.

## Methods

### Aim, objectives and research questions

#### Aim

The aim of the study is to understand health system factors for improving equitable access to quality generic medicines for patients suffering from non-communicable diseases in a rural Indian district.

#### Objectives

To understand if (and how) availability of drugs at government primary health centres (PHC) could be improved through formation of patient groupsTo understand if (and how) utilisation, compliance and quality of care for NCD at government primary health centres could be improved through training PHC staff and optimising existing service-delivery arrangements.To estimate the additional costs for increasing rational use of medicines and services optimisation at PHCsTo understand the health system factors that influence utilisation of drugs at government primary health centresTo document the effects on the private sector of improved drug availability and utilisation in PHCs

#### Research questions

The main research question of the study is: *does a package of interventions involving health services optimisation and strengthening community participation platforms at primary care level improve availability*, *affordability*, *utilisation and compliance of good quality generic drugs for NCDs in government facilities in Karnataka*? *If yes*; *how*, *and for whom and under what conditions does this happen*? We further developed five specific sub-questions in line with the main research question (and our study objectives listed above) as follows:Does optimisation of health services (announcing monthly NCD clinic days, increasing consultation time, providing counselling services and ensuring continuity of care) improve utilisation of drugs and their compliance among patients with NCDs?How can existing community participation arrangements be strengthened to form pressure groups of patients with chronic diseases at PHCs? Does this improve availability of drugs at these PHCs?If NCD patients shift or opt for public sector generic drugs for NCD care, will their OOP expenditure on NCD medicines and proportion of total household expenditure (THE) spent on NCD drugs decrease?Does the routine monitoring of the quality of NCD drugs strengthen the regulation of other drugs? How does the quality of drugs provided in government hospitals compare with those commonly bought over-the-counter in private pharmacies?How do private pharmacies respond to improved generic drugs availability and utilisation in government PHCs? Do the mean prices of essential NCD drugs and their availability change in response to improved availability of these in PHCs?What is the marginal cost of strengthening health systems so that access to medicines can be improved?

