**Fig. 5 Fig5:**
[figure not shown]
ATM conceptual framework

Of the seven *talukas* which qualified for the intervention, we randomly chose three *talukas* using the online random number generating tool (Available at http://www.random.org/; see Additional file 2). The three *talukas* chosen were Koratagere, Sira and Turuvekere. Some characteristics of the three *talukas* are presented in Table 2. PHCs across the three *talukas* were randomly assigned to one of three arms (A, B and C) of the study intervention. In Arm A, PHCs will receive a package of interventions to optimise service delivery, while Arm B, they will receive Arm A package as well as an additional package of interventions to strengthen existing community participation platforms for organising NCD care at PHC. PHCs in Arm C will be the control. The package of activities in A, B and C are described in Table 3. A detailed description of the intervention and the underlying assumptions behind the activities proposed is provided in Additional file 3 and step-wise plan of rolling out of the intervention is presented in Fig. 6.

**Table 2 Tab2:** Characteristics of study talukas

Characteristics	Koratagere	Sira	Turuvekere
Area	652 Sq km	1552 Sq km	778 Sq km
Population	160,952	301,473	174,297
Number of private pharmacies	19	30	22
General adult literacy rate	71 %	67 %	73 %
Number of PHCs	11	17	11
Average population per PHC	14,500	18,000	16,000
Number of private hospitals/clinics	21	64	18
Number of PHCs with qualified MBBS doctors (of) total number of PHCs in *taluka* (as on March 2014)	11 of 11	15 of 17	10 of 11

(Source: Census 2011)

**Table 3 Tab3:** Description of activities planned under the study intervention arms

Intervention arm	Intervention name	Intervention input	Activities
A	Optimise service delivery	Orientation training & workshop for PHC medical officers	Training on standard treatment guidelines for NCDs, rational prescription, maintaining treatment cards for patients with NCDs and conduction of health days for NCD care.
		Training workshop for pharmacists	Training on need assessment for medicines, counselling patients on medicines and their side effects and non- drug treatment, indenting for medicines and record keeping at PHCs.

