		Training workshop for ANMs, ASHAs and Anganwadi workers.	Orientation on lifestyle modification for NCD, need for long-term follow-up and medication for NCD, availability of free generic medicines for NCD at local PHCs and ensuring that patients visit the PHC regularly for follow-up and medicines.
		Advocacy and coordination.	Coordination and advocacy at state, district and taluka levels with different stakeholders to ensure supply of drugs to the PHCs through routine supply chain, district PIP or utilising local funds (ARS).
B	(Optimise service delivery) + Strengthen existing community participation through patient groups and ARS	Development and dissemination of awareness material.	Awareness material shall focus on lifestyle modification for NCD, need for long-term follow-up and medication for NCD, and availability of free generic medicines for NCD at local PHCs. Disseminate material among health workers, local community groups (ARS, VHSC).
		Formation of NCD patient groups.	To organise NCD patients group meeting and inform about the importance of regular treatment and the advantages of generic medicines
		BCC at community level.	Health worker spreading information leaflets about diabetes & hypertension, about the designated NCD check up day event held 1–3 times per year at the PHC. Information on NCD control will also be displayed at prominent places in the PHC and local villages
		Meeting with ARS members.	Orientation of ARS members about their functions and possibility of utilizing untied funds for purchasing medicines for NCD and facilitate their interaction with patient groups and PHC staff
C (Control)	No intervention	Government existing programme for NCD control at primary health centres.	Government’s making effort at improving generic drug availability. Private pharmacies cater to many NCD patients.

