##### End-line survey

After 18 months of the intervention, the survey will be conducted in the same three talukas. The same households (panel survey) that participated in the baseline survey will be visited again with the survey questionnaire.

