#### Process documentation

Process documentation forms an integral part of the qualitative component of this study. Quarterly field visits will be conducted to the PHCs and data on utilisation of various services and medicines dispensed for NCDs will be recorded. The patient experiences, PHC staff attitudes towards NCD patients and details of supervisory visits from taluka health officials would be captured. The latter is in order to understand and interpret possibly taluka-wise differences in local leadership and management that could explain differences in performance between PHCs that have received similar inputs.

The interaction with the providers would focus on the motivating factors in case of early adopters and the perceived difficulty in case of others. After each such visit, a detailed narrative report would be prepared. This report would capture unstructured details about: new changes or updates regarding NCD patients in the PHC, responses of PHC staff to the intervention-related developments such as PHC meetings, sub-centre meetings and PHC health days (in the intervention PHCs). In the control PHCs, the field visits will be used to collect new information on any initiatives to detect or treat NCD patients and perspectives on the staff on NCD care.

As part of the community level intervention, we will participate in the patient group meetings and observe whether the group dynamics and the interaction of the group with the PHC have changed/improved, this will be noted and these groups will be purposively approached during the post-intervention data collection.

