#### Outcome estimation

Outcomes (see Table 9) will be reported as effects of said interventions and represented as risk ratios and odds ratios with 95 % confidence interval.

**Table 9 Tab9:** Measures (indicators) for primary and secondary outcome of interest

Factors to be measured	Indicator
Primary outcome of interest	
Improved and continuous availability of generic drugs at PHC	Percentage of PHC where all generic medicines for NCD patients adequately available in last three months
Increased and regular access to quality medicines for patients with NCD	Percentage of NCD patients/patient groups visit intervention PHC in last three months
Out-of-pocket expenses among patients with NCD	Percentage reduction in median OOP expenditure on medicines per year among NCD patients.
The marginal cost of the intervention to that of the outcome	Incremental cost effective ratio
Improved compliance to standard treatment guidelines by the PHC	Percentage MOs followed prescription practices as per the standard treatment guidelines.
Improved demand of generic drugs among the patients	Percentage increase in patients availing generic drugs from the PHC compared to what it was at three months back
Improved utilization of medicines among NCD patients	Percentage of NCD patients/ patient groups obtained complete and regular medication for last three months.
Secondary outcome of interest	
Better coordination among health staffs with regards to NCD patient group formation	- Percentage increase in number of patient groups formed. - Percentage increase in number of new diabetes patients registered in last three months for a given PHC. - Percentage increase in number of new hypertension patients registered in last three months for a given PHC.
Better drug procurement	Percentage PHCs where drug procurement is up to date for the last quarter.
Conduction of NCD clinics	Percentage PHCs conduct NCD days in last three months
Better reporting and recording by the pharmacists at PHC	Percentage PHCs where medicines were dispensed as prescribed

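### The secondary indicator for NCD days, a three-month yes/no per PHC, fits neither frequency the article gives (monthly, or 1–3 times a year); a count of days held would serve better on either reading

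*Protocol article*

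**What the plan says.** Four places in the protocol article bear on how often NCD days are held.

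- Research questions, first sub-question: optimising health services includes "announcing monthly NCD clinic days".
- Table 3, Arm A, training of medical officers: the training covers "conduction of health days for NCD care". No frequency is given.
- Table 3, Arm B, community-level communication: health workers distribute leaflets, among other things "about the designated NCD check up day event held 1–3 times per year at the PHC". This is the only frequency in Table 3.
- Process documentation: the narrative reports will cover staff responses to developments such as "PHC health days (in the intervention PHCs"). Again no frequency is given.

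Table 9 has one secondary outcome on this activity. Its row label is "Conduction of NCD clinics" and its indicator is "Percentage PHCs conduct NCD days in last three months". It sets no minimum number of days, and the article does not say how often the indicator is read.

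Two further statements matter for the remedy. On follow-up: "After 18 months of the intervention, the survey will be conducted in the same three talukas". On process data: "Quarterly field visits will be conducted to the PHCs and data on utilisation of various services and medicines dispensed for NCDs will be recorded". The same section makes clear that the field visits also cover control PHCs, where they gather information on any initiative to detect or treat NCD patients.

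**The concern.** A yes/no over three months is informative only if the planned frequency makes a yes and a no mean different things. If several days are planned in each window, almost any activity gives a yes, and the indicator saturates. If less than one day is planned per window, a no is often what full compliance looks like. The two frequencies in the article fall on either side of this.

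The study wants to explain why the intervention worked in some PHCs and not in others, so it needs to know how much of the intervention each PHC delivered. This row is the only one in Table 9 that records whether NCD days took place. The narrative reports add evidence on delivery, but the article does not describe them as giving a count that could be set against a plan.

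**Working it through.** The plan gives no figure for this outcome, so there is nothing to reproduce. The check asks what the indicator would show under each stated frequency.

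**Inputs from the article.** Monthly clinic days (Research questions); 1–3 events a year (Table 3, Arm B); a three-month window with no minimum count (Table 9); 18 months of intervention (End-line survey); quarterly visits (Process documentation).

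**Days planned.**

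| Schedule | In 18 months | In a three-month window |
|---|---|---|
| Monthly | 12 × 1.5 = 18 | 12/4 = 3 |
| 1 a year | 1 × 1.5 = 1.5 | 1/4 = 0.25 |
| 2 a year | 2 × 1.5 = 3 | 2/4 = 0.5 |
| 3 a year | 3 × 1.5 = 4.5 | 3/4 = 0.75 |

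The two descriptions differ by a factor of 12/3 = 4 to 12/1 = 12.

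**Monthly reading.** A PHC that holds one day in each quarter delivers 6 of 18 days (33%) and scores yes every time, exactly like a PHC that delivers 18 of 18. As an illustration, suppose each planned day is held independently with probability p. Then P(yes) = 1 − (1 − p)³, and the chance that all three days were held is p³.

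| p (assumed) | Scores yes | All three held |
|---|---|---|
| 1/3 | 1 − (2/3)³ = 70% | 4% |
| 1/2 | 1 − (1/2)³ = 88% | 13% |
| 3/4 | 1 − (1/4)³ = 98% | 42% |
| 1 | 100% | 100% |

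No compliant PHC is missed, but PHCs delivering half or three-quarters of the plan are hard to tell from those delivering all of it.

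**Reading of 1–3 a year, one look-back.** Assume full compliance and a look-back date unrelated to the schedule. With k evenly spaced days a year, a three-month window holds at most one day, so P(no) = 1 − k × 3/12. With k random dates, P(no) = 0.75^k.

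| k | No, evenly spaced | No, random dates |
|---|---|---|
| 1 | 75% | 75% |
| 2 | 50% | 56% |
| 3 | 25% | 42% |

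**Reading of 1–3 a year, read at each quarterly visit.** The 18/3 = 6 windows cover the whole period, so no day is missed. With even spacing, a fully compliant PHC still scores yes in only 6 × k/4 = 1.5, 3 or 4.5 of the 6 quarters on average, and the article states no expected share to compare this with.

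**The case against.** The strongest reply is that no contradiction has been shown. Clinic days appear under service optimisation, which is the Arm A package that Arm B also receives. The check-up event appears only in the additional Arm B communication row. A monthly clinic and an occasional check-up event can coexist, and Additional file 3, which the article cites for the detailed intervention and which is not at hand, may say so. The row label in Table 9 also points to the clinic, and a three-month window is used elsewhere in that table. On that reading no compliant PHC is missed, and treating one day like three is simply what a coverage percentage does.

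Most of this stands. A reader might infer that the article contradicts itself, or that it is at fault merely for not naming the event counted. The documents do not support either: two activities are possible, the label favours one of them, and a supplementary file may settle the matter. A reader might also infer that compliant PHCs will be recorded as failures. That needs the less likely reading, together with a single look-back on an unrelated date, which the article does not state.

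The reply does not rescue the indicator as a measure of delivery. Additional file 3 could settle the frequency, but it would not change the indicator printed in Table 9. On the favoured monthly reading that indicator still saturates, and a count would show what it hides. The planned narrative reports follow health days, but not as a stated count.

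**Conclusion.** The point holds as a minor, cheap improvement. The article gives two frequencies that need to be aligned or separated, and the three-month yes/no suits neither. On the monthly reading, one-third delivery can score the same as full delivery. On the other reading, a single look-back would miss a compliant PHC in roughly 25–75% of cases.

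The equality of 6 of 18 and 18 of 18 needs only that the six days fall one in each window. The other percentages are illustrations: they rest on assumed probabilities of holding a day, independence between days, even or random spacing, full compliance in the 1–3 a year case and, for the 25–75%, one reading on a date unrelated to the schedule.

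It would be wrong to extend this to the main results. It concerns how one secondary delivery outcome is measured and compared between arms; no primary outcome and no sample size figure depends on it.

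**What to change.** 1. If the Research questions and Table 3 mean the same event, correct whichever frequency is wrong. If they mean two events, name both, say which arm each belongs to, and state which one Table 9 counts.
2. At each quarterly visit, in intervention and control PHCs alike, record the number of NCD days held since the last visit.
3. Report days held per PHC over the 18 months, set against days planned in the intervention arms, and compare arms on the rate of days held per PHC.
4. Keep the three-month percentage beside it, labelled as a coverage figure.

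The cost is a wording correction, one outcome definition and one extra field in the visit record, with no new survey. The drawback is that the count relies on how well PHCs record past days.
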